## Abstract

**Background:**

Cognitive fatigue (CF) is a human response to stimulation and stress and is a common comorbidity in many medical conditions that can result in serious consequences; however, studying CF under controlled conditions is difficult. Immersive virtual reality provides an experimental environment that enables the precise measurement of the response of an individual to complex stimuli in a controlled environment.

**Objective:**

We aim to examine the development of an immersive virtual shopping experience to measure subjective and objective indicators of CF induced by instrumental activities of daily living.

**Methods:**

We will recruit 84 healthy participants (aged 18-75 years) for a 2-phase study. Phase 1 is a user experience study for testing the software functionality, user interface, and realism of the virtual shopping environment. Phase 2 uses a 3-arm randomized controlled trial to determine the effect that the immersive environment has on fatigue. Participants will be randomized into 1 of 3 conditions exploring fatigue response during a typical human activity (grocery shopping). The level of cognitive and emotional challenges will change during each activity. The primary outcome of phase 1 is the experience of user interface difficulties. The primary outcome of phase 2 is self-reported CF. The core secondary phase 2 outcomes include subjective cognitive load, change in task performance behavior, and eye tracking. Phase 2 uses within-subject repeated measures analysis of variance to compare pre- and postfatigue measures under 3 conditions (control, cognitive challenge, and emotional challenge).

**Results:**

This study was approved by the scientific review committee of the National Institute of Nursing Research and was identified as an exempt study by the institutional review board of the National Institutes of Health. Data collection will begin in spring 2021.

**Conclusions:**

Immersive virtual reality may be a useful research platform for simulating the induction of CF associated with the cognitive and emotional challenges of instrumental activities of daily living.

**Trial Registration:**

ClinicalTrials.gov NCT04883359; http://clinicaltrials.gov/ct2/show/NCT04883359

**International Registered Report Identifier (IRRID):**

PRR1-10.2196/28073

## Introduction

### Background

The application of digital technologies to improve the monitoring and treatment of chronic clinical conditions is an emerging field in medical research and practice. At the most basic level, the maintenance of and nearly instantaneous access to medical records facilitates tracking and coordination of care among providers is an example of how digital technologies have directly influenced the practice of medicine. The steady increase in apps and digital devices developed to track health-related behaviors and monitor physiological data is a testament to the interest and potential powerful role that technology will play in the future of medicine. These tools may become most useful for aiding health care in the gaps between formal treatment (eg, hospital, clinic, and doctor visit) and day-to-day living in extended or chronic conditions. For example, individuals with chronic medical conditions often experience significant symptoms of cognitive fatigue (CF); however, it is a challenge for clinicians to evaluate the impact of this symptom on daily activities. Technological solutions potentially provide greater insight into the impact of symptomatology on the quality of life. Researchers and clinicians alike have a profound interest in technology and its current and future role in health care delivery.

### Immersive Virtual Reality

Immersive virtual reality (VR) technology has been increasingly used by researchers in many fields as a tool to observe and measure the responses of individuals to complex stimuli in a controlled environment [1-3]. Auditory and visual stimuli induce the sense that they are in a space different from where their physical body is located. Usual tasks (locomotion, pointing, and grasping) are accomplished in a modified manner using ancillary equipment (eg, hand controllers and sensor gloves). Immersive VR environments enable researchers to study psychological phenomena that are more closely connected to the subjective experience of an individual (eg, a tall building to elicit fear) to recreate situations that elicit symptoms (eg, anxiety) or measure specific skills (eg, a kitchen to evaluate home safety). VR environments have been used to evaluate human and environmental factors associated with performing important instrumental activities of daily living (IADLs) such as driving [4], navigating public transportation [5], cooking [6], social relatedness [7], and grocery shopping [8]. The relative advantage of virtual environments over physical spaces is the ability to safely expose individuals to situations that may pose a risk in real life (eg, driving while distracted) and the ability to create controlled environments that would be extremely difficult to duplicate in a consistent, standardized fashion in real-life simulations.

### Implications of CF

CF is a common human experience that can result in serious negative consequences, such as mistakes [9,10] and accidents [11-13]. Although most healthy people experience some degree of CF at varying times, CF can become a debilitating and life-altering experience for individuals diagnosed with chronic medical conditions [14-16]. Debilitating levels of CF occur as a frequent comorbid symptom in a range of medical [17], neurological [18], and acquired conditions [19], particularly those affecting the integrity of neuronal processes [20,21]. The serious consequences of CF at work, during daily activities, and as a potential cause of disability across a broad spectrum of clinical conditions make the study of objective and subjective fatigue in healthy and clinical populations a priority across multiple disciplines.

### CF Induction

The most well-established model for inducing CF under experimental conditions is prolonged cognitive performance. Specifically, participants perform a cognitive task for an extended period (eg, 15-120 minutes) and assessments of fatigue level occur before, during, and after the fatiguing task. Various cognitive tasks reliably induce subjective feelings of fatigue, including continuously performed attention [22,23], inhibition [20,24,25], working memory [26-28], and complex cognitive activities [29-31]. Tasks requiring continuous visual monitoring for *critical events* produce a highly replicable phenomenon called the *vigilance decrement* [32], which has a moderate effect size [33]. Factors affecting the onset of vigilance decrement include image quality [34], response frequency [35], rest breaks and secondary task interruption [36], and multitasking [37]. Moderately complex cognitive functions such as working memory [27,38-41] and inhibitory control [24,42-48] tasks produce subjective feelings of fatigue but inconsistently produce performance decrements. Simple and complex vigilance tasks produce CF; however, these laboratory tasks may not best represent how CF occurs in daily life as boredom and task disengagement may account for observed vigilance decrement effects [38]. A better approach to understand CF for clinical purposes may require the evaluation and assessment of fatigue in typical daily living activities.

### Work Task and Environment Characteristics and CF

Work fatigue studies target tasks and environmental characteristics that produce CF in everyday activities. Close visual work involving inspection, comparison, or identification of details on visual images [49-53] and high rates of decision-making are sources of work fatigue [54-56]. Work interruptions interfering with workflow increase feelings of frustration [57], stress [58], and feelings of emotional exhaustion [59]. Work interruptions cause a loss of focus [60] and increase cognitive workload [61], mental effort, annoyance, frustration, and sense of time pressure [62,63]. Random, uncontrollable, interruptions in the middle of a task [61,62] that require immediate attention induce the most stress [62-64]. Individual differences in personality impact the level of perceived stress and fatigue associated with work-related tasks [63]. Work requiring intensive visual inspection or high rates of decision-making induce fatigue, and environmental factors such as distractions and interruptions significantly increase perceived frustration, workload, and fatigue.

### Daily Living and CF

Managing complex activities, such as shopping, cooking, using transportation, driving, and finances is referred to as an IADL [65]. Extensive research has focused on the relationship between driving and CF. Fatigue and cognitive workload increase with driving [66,67]. Time to fatigue while driving is hastened by extra cognitive demands, stress, distractions, multitasking, and environmental factors [66-68], although time on task and monotony are most impactful [69,70]. Personal characteristics associated with driving fatigue include fatigue proneness, dislike of driving, and coping style [66]. Surprisingly, few studies have evaluated the relationship between IADLs and CF; however, such assessments offer tremendous potential for discerning points for clinical intervention. There is some evidence that apathy, depression, and impaired cognitive functioning are risk factors for difficulties in performing IADLs [71,72]. A public transit study demonstrated that a common IADL induces cognitive workload in real life, task experience moderates perceived workload, and immersive VR provides a close approximation of the cognitive effects observed in real life [5]. The extended performance of a daily activity may induce CF, and the effects are moderated by individual and environmental factors. Grocery shopping provides an apt task for assessing CF.

### Immersive VR and Grocery Shopping

Virtual shopping environments have been used to evaluate how cognitive functions might operate in real-life situations [73-75] and may prove effective for the study of CF. Grocery shopping requires a combination of low and high levels of cognitive processes [8,73-75]. Looking for a specific product requires visual inspection, scanning, and focused attention. Traversing a shopping store requires visual attention (eg, looking for signs), spatial mapping, working memory, memory, and executive functioning [8,73-77]. Virtual shopping environments have been used successfully among individuals with significant cognitive impairment [8,78-81], and virtual shopping tasks correlate with real-life shopping activities [81,82].

We identified immersive VR grocery shopping as a suitable model to study fatigue associated with an IADL because it provides familiar but complex visual stimuli, affords the opportunity to search and choose, and presents the participant with well-known but complex cognitive challenges, such as comparisons, discernment, and decision-making. A potential disadvantage of using immersive VR to study CF is the risk of physical distress and eye strain in VR, which may confound the experience of CF or its measurement [83-85]. The risk of eye strain and other physical symptoms is reduced when high-quality head-mounted display (HMD) devices are used, motion is performed using physical walking or teleporting, the field of view is large, and each eye receives high-quality images [84]. In some cases, the realism of the environment must be sacrificed to reduce side effects.

We propose a 2-phase evaluation of the CF induction in VR. In phase 1, we will explore the feasibility of using immersive VR as a platform for studying CF using a user experience (UX) research methodology. We will use a combination of qualitative and quantitative approaches to identify components of the VR interface or environment that may contribute to feelings of eye strain or distress or make the shopping task difficult to perform. Phase 2 explores cognitive, environmental, and individual characteristics associated with VR-based grocery shopping–induced CF.

### Objectives

Despite extensive research on CF, questions remain regarding the individual and environmental characteristics that relate to CF, particularly in daily living activities. Prior studies evaluating CF in daily activities have primarily focused on driving [5,70] or very specific job-related activities [49,53,86]. We will use immersive VR to control environmental and task characteristics to identify factors that affect the onset of fatigue. Grocery shopping is used as a fatigue-induced activity because it requires multiple simple and complex cognitive functions, has been identified as a significant cause of CF in susceptible individuals [87], and is susceptible to disruption by disability [88]. On the basis of previous research, engaging healthy participants using virtual shopping environments indicates the feasibility and acceptability of VR and therefore provides the best chance of detecting the CF response [5,86,89].

In the experiment, we will replicate numerous cognitive aspects of shopping, including simultaneous and successive engagement of multiple cognitive processes including working memory, spatial planning, inhibitory control, visual search, inspection, and comparison, reading and applying information from nutritional labels, and decision-making. We can manipulate the mental workload through specific task requirements. In addition, we can test the relative effect of environmental factors, such as the effect of sound and visual cues on CF and workload, by introducing the presence of interruptions, distractions, and goal interference. In a controlled shopping environment, where interruptions can be planned carefully, as the participant executes goal-directed behaviors, real-life frustrations such as poor shelf organization and item placement, crowded conditions, noise, and other disruptions can be implemented. In future studies, the virtual shopping environment will allow us to test hypotheses related to the relationship of task difficulty, perceived task difficulty, environmental disruptions, and feelings of frustration with CF. Initial trials will use healthy controls, and subsequent studies will evaluate CF in clinical populations.

The aim of phase 1 is to evaluate the design elements of the virtual shopping environment to identify any factors that may hinder the ability of participants to effectively perform tasks in the virtual environment, identify the risk of physical distress, and obtain user feedback about realism and functionality. The primary hypothesis for the UX study is that the VR environment will be acceptable; however, some users will exhibit minor difficulties using the controllers and interacting with the environment. The primary outcome measures will be observational ratings assessing user difficulties with controller use, interacting with objects, and moving in the environment. The secondary hypotheses include that participants will report only minimal feelings of distress, will report that the virtual grocery store appears realistic and immersive, and will provide a general positive response to the experience with additional helpful ideas about how the experience could be improved.

The primary aim of phase 2 is to evaluate individual and environmental characteristics associated with susceptibility to experiencing CF in the context of performing an IADL, specifically shopping. Our primary hypothesis in phase 2 is that individuals performing structured grocery tasks will report more CF than simple exploratory behavior in the grocery store and that individuals experiencing distractions and interruptions will report more fatigue than those who do not experience interruptions. The primary outcome measure in phase 2 is the self-reported change by participants in CF by shopping experience. The secondary aims of phase 2 are to identify performance and eye-tracking measures that objectively identify fatigue, cognitive abilities, personality characteristics, shopping experience, or transient mood states that affect susceptibility to fatigue during shopping. Specific secondary exploratory hypotheses include that perceived workload increases with time on task for structured tasks and disruptive environments, percent eye closure and gaze shift increase with time on task and are associated with self-reported fatigue, and shopping accuracy declines with time on task.

## Methods

### Study Design

This will be a 2-phase development (UX) and implementation (eg, randomized controlled trial) research protocol. The two phases share the same general immersive VR environment, as shown in Figure 1. The two phases diverged in the non–VR-related procedures used in each protocol. The VR sequence in each phase will follow the standard model commonly used in CF induction studies, that is, baseline cognitive assessment, baseline subjective fatigue and workload assessment, fatigue induction with a midpoint (eg, at 15 minutes) subjective assessment of fatigue, finishing with a postassessment of fatigue, and cognitive assessment. Each of these elements is shown in Figure 1.

**Figure 1 figure1:**
[figure not shown]
Virtual reality content in sequence. NASA-TLX: National Aeronautics and Space Administration–task load index; VAS-F: Visual Analog Scale Fatigue; VR: virtual reality.

Randomization will be used in each study to assign participants to 1 of the 3 grocery shopping experiences: shopping exploration, standard shopping, and shopping interference. In each study phase, participants completed a brief self-reported medical history to rule out conditions associated with chronic fatigue, cognitive impairment, or susceptibility to seizures. Participants in both studies completed the Virtual Reality Symptom Questionnaire (VRSQ) [90] before VR immersion and immediately after VR immersion. These procedures will help differentiate the impact of VR immersion from the fatigue induced by the shopping task.

The phase 1 study will evaluate the participants’ capacity to learn to interact with objects in the virtual environment, navigate within the grocery store environment, read and respond to information and questionnaires, and identify any early adverse effects of VR exposure. The data collected from this study will be used to improve the VR interface and modify the participant interactions or the length of exposure. The study staff will observe the engagement of the participant in the immersive task by viewing the person as well as by viewing their exact point of view on a separate computer screen. Participants will complete rating scales including feelings of presence [91] in the shopping environment, self-reported simulator sickness symptoms [90], and shopping values or experience [92]. All participants completed a standardized UX interview. The phase 2 study protocol, detailed in Figure 2, will incorporate additional self-report and performance measures (see Table 1 for lists of measures in each phase). Additional measures include state and trait measures of fatigue [93,94], current emotional state (ie, anxiety and depression) [94], personality traits [95], and cognitive functioning [96]. These measures will be completed before the VR portion of the study with a 1-hour break between completing additional study measures and VR immersion. Similar to phase 1, participants will complete measures of presence [91] and shopping values or experience [92] to assess the impact of realism, shopping as a pleasant versus utilitarian task, and frequency of grocery shopping in real life on fatigue and performance. A brief post-VR interview will be completed to obtain additional insight about the environment and to debrief participants about the purpose of the study.

**Figure 2 figure2:**
[figure not shown]
Detailed procedure of the cognitive fatigue study. BFI: Big Five Inventory; HMD: head-mounted display; NASA-TLX: National Aeronautics and Space Administration–task load index; NIHTB-CB: National Institutes of Health toolbox–cognition battery; PFS: Pittsburgh Fatigability Scale; PROMIS: Patient-Reported Outcomes Measurement Information System; SDH: social determinants of health; VAS-F: Visual Analog Scale Fatigue; VR: virtual reality.

**Table 1 table1:** Assessments by phase.

Assessments	Phase 1	Phase 2
Virtual Reality Symptom Questionnaire	✓^a^	✓
Immersive VR^b^ cognitive tests	✓	✓
Immersive VR Visual Analog Scale–Fatigue	✓	✓
Immersive VR NASA-TLX^c^	✓	✓
Presence Questionnaire	✓	✓
Shopping Values Questionnaire	✓	✓
Social Determinants of Health	✓	✓
User Experience Interview	✓	
PROMIS^d^ Depression		✓
PROMIS Anxiety		✓
PROMIS Fatigue		✓
Pittsburgh Fatigability Scale		✓
Big Five Inventory		✓
National Institutes of Health Toolbox–Cognition Battery		✓

^a^Assessment is present.

^b^VR: virtual reality.

^c^NASA-TLX: National Aeronautics and Space Administration–task load index.

^d^PROMIS: Patient-Reported Outcomes Measurement Information System.

### Kitchen Tasks

The participants will be seated while performing the tasks in the kitchen environment. The participant will appear to be seated in a kitchen table with a pillbox and pill bottles in front of them. In the first task, the participant will be instructed to correctly select the pillbox compartment (labeled with the days of the week) where each pill belongs. A calendar on the table shows an image of each pill and the pillbox location (eg, Sunday or Monday); when a pill appears in front of the examinee, they will select the correct pillbox location by using a scroll and trigger pull sequence. An animation sequence will show the pill entering the selected location. Another pill will appear with a sound alert until 120 seconds have passed or 120 pills have been sorted.

In the working memory task, the participant will be shown a series of pills by day and time of day associations. Using the same calendar concept, the participant will see where 2 pills are to be placed in the pillbox (eg, red pill in the morning on Monday and blue pill in the evening on Friday) for 10 seconds. They were instructed to remember the location of each pill. The key will be taken out of view and the pills will appear one at a time. Each participant will select the location where each pill belongs using a scroll and trigger sequence. The task will increase in difficulty with 3, 4, 5, and 6, the number of pill locations to recall. The task will end when the participant obtains four consecutive scores of zero.

### Shopping Tasks and Experiences

Participants will remain seated during all VR shopping experiences. Product labels are legible for brands and specific products without selecting the object. Product selection enables the viewing of all product details. Products will be selected off a shelf using a wand controller acting as a pointing device (eg, laser beam), followed by a point, highlight, and trigger pull selection sequence. Selected product labels will appear on a virtual cell phone in front of the participant with a menu of options (eg, buy product, return product, and review shopping list). Participants traverse the store using a restricted teleport feature. Movement will be restricted to a more realistic experience and to avoid long-distance movements that might result in disorientation and difficulties in learning the store layout. Figure 3 presents a screenshot of the grocery store and shows the cell phone, products, and aisle.

**Figure 3 figure3:**
[figure not shown]
Grocery store screenshot.

### Shopping Training

The participant will appear in a small version of the grocery store. They will be instructed on how to use the virtual cell phone to check their shopping list, review items in their cart, and answer text messages with the left-hand controller. They will be instructed on how to teleport and select items off the shelf with the right-hand controller. In the shopping training task, the participant must follow specific directions and must correctly put four items in their cart from the shopping list, one of which must be returned to the shelf, and they must answer a text to complete the shopping training. To complete the shopping portion of the task, the participant will need to teleport successfully to multiple shelves and aisles.

### Shopping Experience Number 1

Experience number 1 will be a control experience that will allow the participant to explore the grocery store with no specific task to complete. The shopping environment includes a few avatars and some low music in the background to simulate a realistic shopping environment during off-hours. All shopping actions will be enabled, and the participant may select items and place them in the shopping cart. The only requirement will be that they remain in the environment for 30 minutes. The control experience will evaluate whether the VR environment itself induces significant fatigue that may confound the interpretation of task-specific fatigue induction.

### Shopping Experience Number 2

Experience number 2 is a standard shopping experience designed to mimic a realistic shopping experience during a typical day. Participants will be provided with a shopping scenario. They will be told that they are shopping for sick friends. The participant will try to obtain as many items as possible from the cell phone shopping list. Participants will traverse the grocery store to find objects on the list and place them in the shopping cart. Avatars are present in the store but do not hinder progress or create any specific distractions. The background sound includes typical background noise, music, and overhead announcements. This condition assesses the cognitive load and fatigue related to the mental activity of shopping.

### Shopping Experience Number 3

Experience number 3 will be the standard shopping experience with frustrating and interrupting events. Participants will be provided the same shopping scenario as experience number 2; however, this shopping experience will be designed to mimic very high traffic, a holiday shopping experience, store crowding, misplaced items, and loud distractions. In addition to environmental stressors, the cell phone will receive *texts* from the friend requesting changes to the grocery list after items have already been selected. Text alerts will be short, repetitive, high-pitched sounds that continue until the text is answered. The progress of the participants will be impeded by an avatar standing in front of a needed item, an aisle blocked for a spill, or a palette blocking access to a specific shelf area. The sounds of a baby crying, people talking, coughing, laughing, and sneezing are present. The music and announcements are played at a slightly higher volume than in the standard shopping condition. This condition will assess the cognitive load and fatigue related to the mental activity of shopping in the presence of distractions and frustrating events.

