For example, we will use the repeated measures ANOVA to test the primary hypothesis that the cognitive activity of shopping for specific items will create a greater perception of mental workload and fatigue compared with just exploring the environment unless the distribution of dependent measures does not allow for using this specific statistical procedure. Similarly, we will use an appropriate correlation procedure to compare the level of activity measures such as distance traversed in the store, number of items selected and reviewed, and efficiency and accuracy of shopping activity with perceptions of fatigue and workload. Correlation procedures will be used to assess the relationships between constructs, such as personality style, cognitive ability, fatigue susceptibility with self-reported mental workload, and fatigue to identify individual differences in fatigue susceptibility. Eye tracking such as percent eye closure will be explored as a possible objective indicator of fatigue by serving as a dependent measure in the repeated measures ANOVA by shopping experience and in correlational analysis with self-reported fatigue and workload. The actual analysis considers the appropriateness for each specific variable distribution.

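### Arms 1 and 2 differ in background sound as well as in task, so the exploration-versus-shopping contrast is a package effect and cannot be credited to the shopping task alone

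*Protocol article*

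**What the plan says.** The Protocol article describes the arms under Shopping Experience Number 1, 2 and 3.

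- **Arm 1 (control).** Participants "explore the grocery store with no specific task to complete". The setting is quiet: "The shopping environment includes a few avatars and some low music in the background to simulate a realistic shopping environment during off-hours". The stated purpose is to see whether the VR environment itself causes fatigue that could confound task-specific fatigue.
- **Arm 2 (standard shopping).** The task is a list: "The participant will try to obtain as many items as possible from the cell phone shopping list". The setting is different: "Experience number 2 is a standard shopping experience designed to mimic a realistic shopping experience during a typical day". On sound, "The background sound includes typical background noise, music, and overhead announcements". On other shoppers, "Avatars are present in the store but do not hinder progress or create any specific distractions". The section then says that this arm assesses load and fatigue from the mental activity of shopping.

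The first part of the primary phase 2 hypothesis (Objectives) is that structured shopping produces more self-reported cognitive fatigue than exploration. The Phase 2 part of the Analysis section states it as a hypothesis about the task: "the cognitive activity of shopping for specific items will create a greater perception of mental workload and fatigue", compared with only exploring.

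**The concern.** The contrast is presented as isolating the cognitive task, but at least one other feature that participants hear throughout the session changes with it. The article does not treat sound as neutral. Objectives says that "we can test the relative effect of environmental factors, such as the effect of sound and visual cues on CF and workload", and arm 3 raises the volume of music and announcements as part of its stress manipulation. If sound may matter between arms 2 and 3, it cannot be assumed inert between arms 1 and 2.

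What is at stake is the meaning of the primary result. A positive arm 2 versus arm 1 difference could come partly from the store and be reported as an effect of the task. The limitations section says that fatigue from the VR environment is the main weakness of the study. Arm 1 is the safeguard against it, yet it presents a quieter store than the one in which arm 2 participants become fatigued.

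**Working it through.** **Step 1: set the two arms side by side.** All entries come from Shopping Experience Number 1 and Number 2.

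| Feature | Arm 1 | Arm 2 | Does it differ? |
|---|---|---|---|
| Task | free exploration | scenario and list | yes, intended |
| Time of day depicted | off-hours | typical day | yes, stated |
| Sound | low music | noise, music and announcements | yes, stated |
| Avatars | a few | present, number not given, said not to obstruct or distract | possibly; inferred only |

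**Step 2: write the contrast.** Let m(t, e) be mean change in fatigue, with t = 0 for exploration and 1 for the list, and e = 0 for the off-hours store and 1 for the typical-day store. Arm 1 estimates m(0,0) and arm 2 estimates m(1,1). Then

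m(1,1) − m(0,0) = [m(1,1) − m(0,1)] + [m(0,1) − m(0,0)].

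The first bracket is the task effect in the typical-day store. The second is the ambient effect without a task. Both need m(0,1), which no arm supplies. The other decomposition needs m(1,0), which no arm supplies either. Arm 3 does not help, because it adds interference events and a still louder, more crowded store to the same task. Task and ambience are therefore fully aliased in the comparison of arms 1 and 2, and the planned repeated measures ANOVA by shopping experience estimates only their sum.

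**Step 3: what is known of the size.** The documents give no ambient effect, and its sign is not certain. The section on daily living says that monotony is among the strongest drivers of driving fatigue, so a livelier store might even reduce fatigue.

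The following is an illustration only. Assumptions: 60 participants split equally (20 per arm; the phase 2 ratio is not stated), two-sided alpha 0.05 (not stated), a two-sample t test on change scores in place of the three-arm ANOVA, a true task effect of zero, and an ambient shift of d SDs. The noncentrality is d × √(20/2) with 38 degrees of freedom.

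| Assumed ambient shift d | Noncentrality | Chance of a significant arm 1 versus arm 2 difference |
|---|---|---|
| 0 | 0 | 5% |
| 0.2 | 0.63 | 9% |
| 0.3 | 0.95 | 15% |
| 0.4 | 1.26 | 23% |

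The planned comparison could not tell these results from a task effect.

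**The case against.** The best reply is that a comparison of whole experiences is legitimate. Randomisation identifies a causal effect of standard shopping against exploration, and the analysis is framed by shopping experience. This stands. A reader might infer that the arm 1 versus arm 2 result could not be interpreted at all, and the documents do not support that. What fails is attribution to the task alone.

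Second, a reader might take it as documented that arm 2 is more crowded. It is not. Neither arm has an avatar count, the inference rests on the time of day depicted, and arm 2 avatars are said not to obstruct or distract. The article gives no such assurance about noise and announcements.

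Third, the sentence in Objectives about sound and visual cues goes on to say that the test works by adding interruptions, distractions and goal interference. That describes arm 3 more than the background of arm 2, and it announces a test rather than an established effect. The section on work fatigue likewise concerns interruptions and distractions, not ambient music. So ambient sound is a plausible rival cause, not a proven one, and the task may well be the larger component.

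Fourth, the planned correlations of shopping activity with fatigue, if examined within arm 2, hold the soundscape constant and give indirect evidence on the task. That evidence is not randomised and does not replace the contrast.

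Fifth, headset, seating and teleport movement are shared, so arm 1 does address eye strain and physical distress from VR. What it misses is the ambient setting of arm 2.

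**Conclusion.** The point holds in this form: arms 1 and 2 differ in background sound by explicit statement, and possibly in avatar density, as well as in task. The contrast estimates a package effect. The wording in Shopping Experience Number 2 and in the Phase 2 analysis, which credits the mental activity of shopping, claims more than the design can show.

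The size is unknown. The 9% to 23% above rests wholly on assumed shifts and on the simplifications listed. A reader might want to take a share of the effect size of 0.65 given under Participants as the amount wrongly credited to the task. The article says only that this value comes from fatigue induction studies using the VAS-F. It does not call it a difference between arms, so no such share can be derived.

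This is worth changing before data collection, because no planned analysis can separate the two components afterwards.

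**What to change.** Run arm 1 in the arm 2 store, with the same avatars, background noise, music level and announcements. Arms 1 and 2 then differ only in the shopping scenario and list, and the contrast becomes m(1,1) − m(0,1), the task effect in that store. Arm 1 would then also show the fatigue produced by the environment that arm 2 uses.

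The cost is small. These are settings in software that the Conclusions section says is still being modified, and no participants, visits or measures are added. The downside is that the control no longer depicts an off-hours store. The change does not touch arm 3, which would still differ from arm 2 in crowding and volume as well as in interference events.

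If the settings are kept, restate the arm 2 versus arm 1 contrast in the hypothesis and analysis text as standard shopping experience versus off-hours exploration, and remove the attribution to the cognitive activity of shopping alone. This costs only wording, but it gives up the isolated task effect.
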